### 2.3. Sample Size and Study Duration

The study is planned to include approximately 100 consecutive eligible patients admitted over a 15-month period. The sample size was estimated based on local patient volumes and previous annual ED statistics (over 600 COPD admissions per year), ensuring sufficient statistical power to detect correlations between biomarker levels and clinical outcomes. Baseline biomarker values will be analyzed exclusively for prognostic correlation with the later need for oxygen therapy, NIV or IMV, and will not be used to guide acute therapeutic escalation or de-escalation.

Based on an estimated annual number of approximately 600 COPD presentations to the ED, we anticipated enrolling around 100 eligible patients meeting the study inclusion criteria. In these participants, five biomarkers (resistin, CC16, IL-6, TNF-α, and S100β protein) will be measured and correlated with disease severity and short-term outcomes.

A post hoc power analysis performed using G*Power software (version 3.1.9.7) for a two-tailed Mann–Whitney test, assuming a large effect size (Cohen’s d = 0.8) and a Bonferroni-adjusted significance level (α = 0.01), indicated a statistical power (1 − β) of approximately 0.91–0.92. This suggests that a sample size of 100 participants could be adequate for detecting large and clinically relevant differences in biomarker levels between well-defined severity or outcome groups. In patients with acute exacerbations of COPD, Vassiliou et al. reported higher serum resistin levels during the acute phase as compared to the stable phase after clinical recovery (median at admission 19.44 ng/mL vs. 9.70 ng/mL at follow-up), indicating a large difference between clinically distinct states [4]. We will reevaluate the sample size after enrollment of 20 patients, and we plan to extend the study to other centers, if necessary.

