#### 2.5.6. Statistical Analysis

All statistical analyses will be performed using appropriate parametric or non-parametric tests, depending on data distribution as assessed by the Shapiro–Wilk test. Descriptive statistics will be used to summarize baseline demographic, clinical, and laboratory characteristics, with results expressed as mean ± standard deviation (SD) or median (interquartile range, IQR) for continuous variables, and as absolute and relative frequencies for categorical variables. Associations between biomarker concentrations and clinical severity scores (SOFA, DECAF, Ottawa COPD Risk Scale, BAP-65, and CFS) will be evaluated using correlation coefficients (Pearson or Spearman, as appropriate). Due to the high heterogeneity of patients with AECOPD in the ED, multivariable analyses will be performed to account for potential confounding factors. Regression models will be adjusted for specific clinical covariates, including demographic characteristics, relevant comorbidities, baseline disease severity indicators, and validated clinical severity scores (SOFA, DECAF, BAP-65, Ottawa COPD Risk Scale, and Clinical Frailty Scale). The number of predictors included in multivariable models will be limited in relation to the number of observed outcome events (approximately 5–10 events per predictor when possible). Effect sizes and confidence intervals will be reported alongside *p*-values to facilitate appropriate interpretation of results. Receiver Operating Characteristic (ROC) curve analysis will be applied to determine the discriminative performance of individual biomarkers, and the area under the curve (AUC) will be calculated to identify optimal cutoff values associated with adverse outcomes. Short-term prognosis will be further analyzed through Kaplan–Meier survival curves and log-rank tests for 28-day mortality. A two-tailed *p*-value < 0.05 will be considered statistically significant for all analyses.

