## Figures and Tables

**Table 1 diagnostics-16-00122-t001:** Objectives proposed by the research team.

Primary Objective	Secondary Objectives
To evaluate the association between serum levels of resistin, CC16, IL-6, TNF-α, and S100β measured at ED admission and early outcomes, including discharge status and 28-day survival, in patients presenting with acute exacerbations of COPD (AECOPD).	To determine biomarker cutoff values associated with the need for escalation of respiratory support (oxygen therapy, non-invasive ventilation, or invasive mechanical ventilation).
	To identify combinations of circulating biomarkers and established clinical scores that best predict short-term mortality and organ dysfunction.
	To assess the relationship between diaphragmatic contractility evaluated by bedside ultrasound and circulating biomarker levels, in relation to the level and duration of ventilatory support.
	To explore the potential role of biomarker-based risk stratification in informing clinical decision-making for AECOPD patients in the ED.

Legend: CC16—club cell secretory protein 16; IL-6—interleukin-6; TNF-α—tumor necrosis factor-alpha; S100β—S100 calcium-binding protein beta; ED—Emergency Department; COPD—chronic obstructive pulmonary disease; AECOPD—acute exacerbation of chronic obstructive pulmonary disease.

**Table 2 diagnostics-16-00122-t002:** Inclusion criteria for eligible study participants.

Inclusion Criteria	
Age ≥ 50 years. Confirmed prior diagnosis of COPD, regardless of disease stage or ongoing therapy:	
(a) the GOLD spirometric grades	GOLD I (FEV_1_ ≥ 80%) GOLD II (50% ≤ FEV_1_ < 80%) GOLD III (30% ≤ FEV_1_ < 50%) GOLD IV (FEV_1_ < 30%)
(b) ABE category assessment	A—low symptom burden and low risk of exacerbations; 0–1 moderate exacerbations in the previous year, with no hospitalizations B—increased symptoms but low risk of exacerbations; 0–1 moderate exacerbations in the previous year, without hospitalization E—high exacerbation risk, defined as ≥ 2 moderate exacerbations or ≥1 exacerbation requiring hospitalization in the previous year, irrespective of the level of symptoms
Admission to the ED with acute exacerbation of COPD. Signed informed consent obtained from the patient or legal representative.	

Legend: COPD—chronic obstructive pulmonary disease; GOLD—Global Initiative for Chronic Obstructive Lung Disease; FEV_1_—forced expiratory volume in 1 s; ED—Emergency Department.

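### Power is calculated at a Bonferroni-adjusted alpha of 0.01, but the analysis section calls every p-value below 0.05 significant, with no multiplicity adjustment

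*Protocol article*

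**What the plan says.** Three places in the protocol article bear on this.

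- **Section 2.3 (Sample Size and Study Duration).** The number of patients comes from local patient volumes. A post hoc power analysis then checks it, "for a two-tailed Mann–Whitney test, assuming a large effect size" (Cohen's d of 0.8) and "a Bonferroni-adjusted significance level (α = 0.01), indicated a statistical power" of about 0.91–0.92. The preceding paragraph of the same section says that "five biomarkers (resistin, CC16, IL-6, TNF-α, and S100β protein) will be measured and correlated with disease severity and short-term outcomes".
- **Section 2.5.6 (Statistical Analysis).** The closing sentence says that a two-tailed p-value "< 0.05 will be considered statistically significant for all analyses". The section mentions no multiplicity adjustment and makes no exception for the primary objective.
- **Table 1 (Objectives).** The primary objective relates all five biomarkers to "early outcomes, including discharge status and 28-day survival". It singles out no lead biomarker and no lead outcome.

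**The concern.** Section 2.3 tells the reader that multiplicity across the biomarkers has been allowed for. Section 2.5.6 removes that allowance at the point where results are judged. For a primary biomarker with, say, p = 0.03, the rule in 2.5.6 gives a significant finding, while the power calculation counts the same result as a failure to reject.

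The type I error behind the quoted power is thus not the one that will be applied. With five biomarkers and up to two outcomes in the primary objective, at least one spurious prognostic marker becomes considerably more likely than the 5% that a Bonferroni correction implies. If the choice is left until the p-values are known, either threshold can be defended by citing a different section.

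**Working it through.** **Inputs.** From 2.3: alpha 0.01, two-tailed Mann–Whitney test, d = 0.8, N = 100, stated power 0.91–0.92, five biomarkers. From 2.5.6: alpha 0.05 for all analyses. From Table 1: two named outcomes. Assumed, because the article does not state it: a 50:50 split between the groups compared.

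**1. Which alpha does the stated power belong to?** The noncentrality is d × √(n₁n₂/(n₁+n₂)) = 0.8 × √(50 × 50/100) = 4.0.

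| Method | Power at alpha 0.01 | Power at alpha 0.05 |
|---|---|---|
| Normal approximation, Φ(4.0 − 2.576) | 0.923 | – |
| Noncentral t | 0.913 | 0.977 |
| Noncentral t, sample size scaled by the Mann–Whitney efficiency 3/π | 0.897 | 0.972 |

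The stated 0.91–0.92 is reproduced at 0.01 and not at 0.05, so the 0.01 in 2.3 is not a misprint. The article does not spell out the divisor, but 0.05/5 = 0.01 and the section names five biomarkers.

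**2. Family-wise error under the rule in 2.5.6.** With k independent tests and every null hypothesis true, it is 1 − (1 − α)^k.

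- Five biomarkers, one outcome, α = 0.05: 1 − 0.95⁵ = 22.6%.
- Five biomarkers, two outcomes, α = 0.05: 1 − 0.95¹⁰ = 40.1%.

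Independence is unlikely here. The markers are largely inflammatory. The outcomes overlap, since 2.5.4 makes death in the ED one of the discharge categories. Simulating correlated normal test statistics (400,000 draws, all nulls true) gives:

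| Family | Assumed correlation | Family-wise error at 0.05 |
|---|---|---|
| 5 tests | 0.3 between markers | 20.9% |
| 5 tests | 0.5 between markers | 18.2% |
| 5 tests | 0.8 between markers | 12.8% |
| 5 × 2 tests | 0.3 between markers, 0.5 between outcomes | 35.2% |
| 5 × 2 tests | 0.5 between markers, 0.5 between outcomes | 31.0% |

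**3. Family-wise error under the alpha in 2.3.**

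- Five tests at 0.01: 1 − 0.99⁵ = 4.9% under independence, and at most 5 × 0.01 = 5% under any correlation.
- Ten tests at 0.01: 1 − 0.99¹⁰ = 9.6%, so a divisor of five does not cover both outcomes.
- Ten tests at 0.005: 1 − 0.995¹⁰ = 4.9%.

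**4. Power if the family is ten.** By the 3/π method with a 50:50 split, power falls from 0.897 at alpha 0.01 to 0.846 at alpha 0.005. Unequal groups lower it further: at alpha 0.01 a 20:80 split already gives only 0.69 (3/π) to 0.72 (noncentral t).

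**The case against.** **The 0.01 is only a planning assumption.** This stands in part. A reader might infer that alpha 0.01 determined the sample size, or that the protocol requires p < 0.01 before a biomarker is called prognostic. Neither is in the article. The number of patients came from admission volumes, 0.01 appears only in the post hoc check, and the only decision rule is the one in 2.5.6. The conflict is between a power assumption and a decision rule. It remains a conflict, because a Bonferroni-adjusted power figure describes tests that the analysis section does not plan.

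**Planning at the stricter level is conservative.** True for power: at 0.05 the same calculation gives 0.972–0.977, so the mismatch does not leave the study underpowered. The cost is entirely in false positives.

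**The error rates are overstated.** The figures of 23% and 40% are ceilings, not estimates, since they need independent tests and no true association for any marker. The ten-test family is also a reading of Table 1, which does not call the outcomes co-primary. A reader might go further and count the five biomarkers against five severity scores (1 − 0.95²⁵ = 72%). Those correlations are not in the primary objective, so that figure says nothing about the primary family.

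**This is an observational study whose results will not guide care, and a fuller analysis plan may settle it.** Section 2.5.6 does promise effect sizes and confidence intervals, which helps interpretation but does not say which threshold applies. Nor is this detail left for elsewhere: two explicit statements in one article disagree, and the wording of 2.5.6 allows no exception.

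**Conclusion.** Wrong as written. The power statement in 2.3 assumes multiplicity control that the decision rule in 2.5.6 does not apply.

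If all nulls are true, the family-wise error at 0.05 is up to about 23% for five biomarkers on one outcome, and about 13–21% for marker correlations from 0.8 down to 0.3. If both named outcomes count, it is up to about 40%, and about 31–35% under the correlations assumed above. The level implied by Bonferroni is 5%, and every scenario examined is well above it.

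The conclusion rests on reading 0.01 as 0.05/5, which the article does not say in words. The ten-test figures also rest on treating discharge status and 28-day survival as both primary, which Table 1 permits but does not state. The contradiction between the two alphas depends on neither assumption.

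**What to change.** Replace the last sentence of 2.5.6 with a rule that matches 2.3.

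- **One primary outcome.** Name it. Test the five novel biomarkers against it with Holm-Bonferroni at family-wise 0.05. The steps are 0.05/5 = 0.01, then 0.0125, 0.0167, 0.025 and 0.05, so the first step equals the alpha in 2.3 and the existing power calculation still corresponds to it.
- **Both outcomes primary.** Define ten tests with a first step of 0.05/10 = 0.005, and restate the power in 2.3: about 0.85 under an assumed 50:50 split, lower if the groups are unequal.
- **28-day mortality.** When this outcome is primary, keep its test inside the primary family. That includes the log-rank test if it is the chosen one, as it is the only test that 2.5.6 names specifically for 28-day mortality.
- **Everything outside the family.** Label it exploratory, with nominal p-values and confidence intervals. Removing the contradiction does not require suppressing those p-values.

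The cost is fewer nominally significant results. Naming a single outcome also means editing the primary objective in Table 1, and keeping both means a new power figure. No change to data collection is needed.

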## 3. Expected Results and Anticipated Discussion

In this study, we expect to identify a composite biomarker profile-combining resistin, CC16, IL-6, TNF-α, and S100β-that improves early prognostic assessment in AECOPD beyond established clinical scores and routine laboratory indicators. It is important to emphasize that biomarker measurements obtained at ED admission are used exclusively as early prognostic indicators. Their purpose is to examine whether higher baseline levels predict progression to supplemental oxygen, NIV, or IMV, without influencing therapeutic decisions during hospitalization.

Three pre-specified findings are anticipated:Early biomarker–outcome correlations.

Higher admission levels of inflammation and injury biomarkers are expected to correlate with the need for ventilatory escalation, prolonged hospital stay, and increased 28-day mortality. Prior studies demonstrated that pro-inflammatory cytokines-particularly IL-6 and TNF-α- rise during acute exacerbations and are associated with clinical deterioration, frequent relapses, and mortality, supporting their role as prognostic markers in acute care models [14,15].

In COPD cohorts, resistin levels increase during exacerbation and decline upon recovery, mirroring systemic inflammatory burden and multi-organ stress [4,5,10,11]. These dynamics suggest its potential as a broad indicator of systemic inflammation in AECOPD [6].

II.Added value over clinical scores.

We expect incremental prognostic accuracy when integrating biomarker panels with validated Emergency Department risk tools such as DECAF [7], Ottawa COPD Risk Scale [9], and BAP-65 [8]. This integration could enhance discrimination and calibration for early triage decisions (e.g., progressive escalation from oxygen therapy to non-invasive ventilation, and ultimately invasive mechanical ventilation) and inform safer de-escalation strategies. While these scores already predict short-term outcomes effectively, adding an objective biological layer may refine their real-time predictive performance and improve individualization of care in the ED.

III.Mechanistic read-outs with management implications.

Lower CC16, a marker of bronchiolar epithelial integrity, has been causally associated with increased COPD susceptibility and faster progression in Mendelian randomization analyses [6]. In the acute setting, reduced CC16 concentrations may reflect extensive epithelial damage and predict more severe trajectories in AECOPD [12,13].

In parallel, S100β may index hypoxic neuro-injury during severe exacerbations. Elevated serum S100β has been linked to cerebral ischemic stress and neuronal damage in acute respiratory and critical illnesses, supporting its potential role as a neuro-systemic prognostic adjunct in the ED [16,17,22,23].

Originality and downstream impact:

To our knowledge, no ED based study has jointly evaluated the prognostic value of resistin, CC16, IL-6, TNF-α, and S100β in patients with AECOPD. Prior studies have assessed these molecules individually or in non-acute contexts, but none have integrated them within a unified, outcome-oriented framework [4,5,6,7,8,9,10,11,12,13,14]. Our study addresses this gap and is designed to derive cut-off thresholds and a parsimonious composite prognostic score applicable to emergency workflows.

If confirmed, these findings will support biomarker-guided algorithms—for instance, thresholds triggering NIV/IMV escalation or identifying extubation readiness when combined with diaphragmatic ultrasound—and may inform future therapeutic trials aimed at modulating inflammatory and epithelial-repair pathways (e.g., anti-TNF agents or CC16-protective interventions).

## Figures and Tables

**Table 1 diagnostics-16-00122-t001:** Objectives proposed by the research team.

Primary Objective	Secondary Objectives
To evaluate the association between serum levels of resistin, CC16, IL-6, TNF-α, and S100β measured at ED admission and early outcomes, including discharge status and 28-day survival, in patients presenting with acute exacerbations of COPD (AECOPD).	To determine biomarker cutoff values associated with the need for escalation of respiratory support (oxygen therapy, non-invasive ventilation, or invasive mechanical ventilation).
	To identify combinations of circulating biomarkers and established clinical scores that best predict short-term mortality and organ dysfunction.
	To assess the relationship between diaphragmatic contractility evaluated by bedside ultrasound and circulating biomarker levels, in relation to the level and duration of ventilatory support.
	To explore the potential role of biomarker-based risk stratification in informing clinical decision-making for AECOPD patients in the ED.

Legend: CC16—club cell secretory protein 16; IL-6—interleukin-6; TNF-α—tumor necrosis factor-alpha; S100β—S100 calcium-binding protein beta; ED—Emergency Department; COPD—chronic obstructive pulmonary disease; AECOPD—acute exacerbation of chronic obstructive pulmonary disease.

**Table 2 diagnostics-16-00122-t002:** Inclusion criteria for eligible study participants.

Inclusion Criteria	
Age ≥ 50 years. Confirmed prior diagnosis of COPD, regardless of disease stage or ongoing therapy:	
(a) the GOLD spirometric grades	GOLD I (FEV_1_ ≥ 80%) GOLD II (50% ≤ FEV_1_ < 80%) GOLD III (30% ≤ FEV_1_ < 50%) GOLD IV (FEV_1_ < 30%)
(b) ABE category assessment	A—low symptom burden and low risk of exacerbations; 0–1 moderate exacerbations in the previous year, with no hospitalizations B—increased symptoms but low risk of exacerbations; 0–1 moderate exacerbations in the previous year, without hospitalization E—high exacerbation risk, defined as ≥ 2 moderate exacerbations or ≥1 exacerbation requiring hospitalization in the previous year, irrespective of the level of symptoms
Admission to the ED with acute exacerbation of COPD. Signed informed consent obtained from the patient or legal representative.	

Legend: COPD—chronic obstructive pulmonary disease; GOLD—Global Initiative for Chronic Obstructive Lung Disease; FEV_1_—forced expiratory volume in 1 s; ED—Emergency Department.

**Table 3 diagnostics-16-00122-t003:** Exclusion criteria for eligible study participants.

Exclusion Criteria	
Age < 50 years. Coexisting acute or chronic conditions that could influence respiratory failure:	
(a) respiratory infections without underlying COPD	pneumonia, acute bronchitis, acute pulmonary viral infections (influenza, RSV, SARS-CoV-2, etc.)
(b) respiratory non-COPD causes	pneumothorax, asthma, bronchiectasis exacerbation in the absence of COPD), cystic fibrosis, upper airway obstruction (tumor, foreign body, laryngeal edema), hyperventilation syndrome or panic attack
(c) acute exacerbation of pre-existing interstitial lung disease (ILD)	idiopathic pulmonary fibrosis, interstitial pneumonias associated with connective tissue diseases, sarcoidosis, hypersensitivity pneumonitis, drug- or radiation-associated ILD
(d) cardiac causes	acute heart failure, acute coronary syndromes, cardiac tamponade, clinically significant arrhythmias, cardiogenic shock
(e) thromboembolic disease	pulmonary embolism
(f) metabolic or systemic causes	metabolic acidosis (DKA, renal failure), severe anemia, sepsis from non-pulmonary sources, hypovolemic shock, anaphylactic shock
(g) trauma	burns or trauma of any localization
(h) neurological conditions affecting respiratory function	acute stroke, neuromuscular diseases causing respiratory depression (myasthenia gravis, Guillain-Barré syndrome, amyotrophic lateral sclerosis)
Pregnancy. Cardiac arrest prior to or during ED admission. Terminal—stage neoplastic disease. Patients under custodial measures or unable to provide consent. Failure to obtain informed consent.	

Legend: COPD—chronic obstructive pulmonary disease; RSV—respiratory syncytial virus; SARS-CoV-2—severe acute respiratory syndrome coronavirus 2; ILD—interstitial lung disease; DKA—diabetic ketoacidosis; ED—Emergency Department.

**Table 4 diagnostics-16-00122-t004:** Analytical Performance and Reference Values of the Selected Biomarkers.

Biomarker	ELISA Kit (Elabscience®, Biotechnology Inc., Wuhan, Hubei, China)	Detection Range (Units)	LOD/Sensitivity (Units)	CV% (Intra/Inter)	Specificity/Cross-Reactivity	Normal Values (Adults)
Resistin	Human Resistin ELISA Kit (E-EL-H1213)	0.31–20 ng/mL	<0.19 ng/mL	<10%/<12%	High analytical specificity; no detectable cross-reactivity with other adipokines	3–12 ng/mL; higher in smokers and older adults
CC16	Human CC16 ELISA Kit (E-EL-H6083)	0.78–50 ng/mL	<0.47 ng/mL	<10%/<12%	No detectable cross-reactivity with other secretoglobins (SCGB family)	4–10 ng/mL in non-smokers; up to 15 ng/mL in smokers
IL-6	Human IL-6 ELISA Kit (E-EL-H6156)	7.81–500 pg/mL	<4.69 pg/mL	<10%/<12%	Minimal cross-reactivity; no measurable interference with IL-1β, IL-8, TNF-α, IFN-γ	<5–7 pg/mL; age-related increase possible
TNF-α	Human TNF-α ELISA Kit (E-EL-H0109)	15.6–1000 pg/mL	<9.38 pg/mL	<10%/<12%	High specificity; no detectable cross-reactivity with TNF-β or related cytokines	<8–10 pg/mL
S100B	Human S100B ELISA Kit (E-EL-H1297)	15.6–1000 pg/mL	<9.38 pg/mL	<10%/<12%	No measurable cross-reactivity with S100A1, S100A8, or other calcium-binding proteins	<90–100 pg/mL in healthy adults

Legend: ELISA—enzyme-linked immunosorbent assay; LOD—limit of detection; CV—coefficient of variation; ng—nanogram; CC16—club cell secretory protein 16; SCGB—secretoglobin protein family; IL-6—interleukin-6; pg—pictogram; IFN-γ—interferon gamma; TNF-α—tumor necrosis factor-α. Analytical specificity is reported as provided by the manufacturer, indicating absence of detectable cross-reactivity with structurally related proteins.

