#### 2.5.3. Biomarkers Selected for Assessment in the Study

Serum concentrations of resistin, CC16, IL-6, TNF-α and S100B protein will be measured using standardized sandwich ELISA assays kits (Elabscience^®^, Biotechnology Inc., Wuhan, Hubei, China). Blood samples will be collected at ED admission into 5 mL biochemistry vacutainers with gel separator. After collection, samples will be centrifuged, at 3500 rpm and the resulting serum will be either processed fresh within a maximum of eight hours or stored at −70 °C until analysis, according to the manufacturer’s recommendations. Hemolyzed or lipemic samples will be excluded.

All assays will be performed following the manufacturer’s protocol, including reagent preparation, incubation conditions, calibration curve generation, and internal quality control verification. Optical density will be measured at 450 nm, and biomarker concentrations will be calculated using a four-parameter logistic (4-PL) curve model.

The analytical characteristics of each ELISA assay, detection range, analytical sensitivity (LOD/LOQ), intra- and inter-assay variability (CV%), assay specificity and cross-reactivity, and reference intervals for normal adult populations, are summarized in Table 4.

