#### 2.5.4. Data Monitoring

At ED admission, all patients will undergo assessment using validated severity and prognostic scores available on the MDCalc platform (www.mdcalc.com). The following tools will be applied: mMRC Dyspnea Scale for grading dyspnea severity, the SOFA score, GCS, for evaluating neurological impairment secondary to hypoxia or hypercapnia, and the CFS, adapted for triage levels used in Romania, to estimate frailty and predict mortality. Additional prognostic scores specific to COPD will be applied, including the Ottawa COPD Risk Scale (predicting 30-day mortality or severe adverse events such as myocardial infarction or the need for intubation), the DECAF Score for in-hospital mortality in acute exacerbations of COPD, and the BAP-65 Score for in-hospital mortality prediction.

Serum biomarker levels will be measured according to the previously described analytical protocol. Based on clinical status and therapeutic requirements, study participants will be classified into three groups: COPD patients requiring supplemental oxygen therapy, those requiring NIV, and those requiring IMV. These measurements are intended solely to establish prognostic associations with subsequent respiratory support requirements and will not influence real-time clinical management.

At discharge from the ED or before hospitalization in the Pulmonology Department or the Internal Medicine Department, patient outcomes will be documented as improved (reduction in dyspnea and clinical instability, no requirement for escalation of respiratory support, decreased level of respiratory support, and evidence of improving gas exchange), stable (no significant improvement but no deterioration, with the same level of respiratory support maintained), worsened (increased respiratory distress, need for escalation of respiratory support, and worsening gas exchange or hemodynamics), or deceased (ED mortality). The total duration of hospitalization will be recorded, as well as survival time, including the date of death if it occurred during the ED stay or hospitalization. Early survival will additionally be assessed at 28 days through telephone follow-up.

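### The cardiac-arrest exclusion is not limited to arrests before the baseline sample, so as worded it can exclude patients whose death in the ED the protocol counts as an outcome

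*Protocol article*

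**What the plan says.** Four parts of the protocol article bear on this point.

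- **Eligibility (Table 3).** One exclusion criterion reads "Cardiac arrest prior to or during ED admission". It does not refer to the blood sample, consent or enrolment.
- **Baseline (Section 2.5.3).** "Blood samples will be collected at ED admission into 5 mL biochemistry vacutainers with gel separator".
- **Outcome (Section 2.5.4).** Status on leaving the ED is recorded in four levels: improved, stable, worsened, "or deceased (ED mortality". Survival time is recorded too, "including the date of death if it occurred during the ED stay or hospitalization". Then: "Early survival will additionally be assessed at 28 days through telephone follow-up".
- **Objective and analysis (Table 1, Section 2.5.6).** The primary objective relates the admission biomarkers to "early outcomes, including discharge status and 28-day survival". The analyses include Kaplan–Meier curves and log-rank tests for 28-day mortality, and ROC curves with cut-offs for adverse outcomes.

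No section says what happens to a patient who is sampled on arrival and arrests later in the ED.

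**The concern.** In a prognostic cohort, membership should be settled by what is known at baseline. Here the baseline is the sample at ED admission, and prediction runs forward from it. An exclusion that can be triggered after that sample, by an event that commonly precedes death, selects on the outcome.

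Taken literally, a patient who is sampled, deteriorates, arrests and dies in the ED meets an exclusion criterion and is also an outcome event. If the exclusion prevails, the deaths lost are the earliest ones. Patients who survive an arrest in the ED are lost as well, although many of them would fall under the existing worsened level. Mortality would be understated, and the biomarker associations, AUCs and cut-offs would describe a cohort from which early collapse has been removed. That matters for a study whose stated purpose (Section 3) is thresholds and a score for use in emergency work.

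**Working it through.** **1. The passages side by side**

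| Course of the patient | Table 3, *during* = whole ED stay | Table 3, *during* = at arrival | Section 2.5.4 |
|---|---|---|---|
| Arrest before arrival | Excluded | Excluded | Not applicable |
| Sampled, then arrests and dies in the ED | Excluded | Kept | Deceased; date of death recorded |
| Sampled, arrests in the ED, survives | Excluded | Kept | Would normally be worsened; followed to 28 days |
| Sampled, dies in the ED, no arrest recorded | Kept | Kept | Deceased |
| Dies after leaving the ED, within 28 days | Kept | Kept | Death in 28-day survival |

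The two readings differ in the second and third rows only. On the first reading those rows conflict with Section 2.5.4; on the second they do not. The abstract describes the discharge status as that at hospital discharge, while Section 2.5.4 defines it on leaving the ED. The conflict does not depend on this, because a death in the ED is a death within 28 days either way.

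**2. What the protocol quantifies**

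It gives no mortality rate, no number of ED deaths and no share of ED deaths that involve an arrest, so there is no figure of its own to reproduce on this point. Its one power figure (Section 2.3: 0.91–0.92 for d = 0.8, α = 0.01, 100 patients) does reproduce if the groups are 50:50. The non-centrality is 0.8 × √(50 × 50 / 100) = 4.0, and the non-central t distribution gives 0.91. That figure says nothing about selection.

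**3. Illustration of lost deaths (all inputs assumed)**

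Let *m* be 28-day mortality and *s* the share of deaths that are arrests in the ED after sampling. Per 100 sampled patients:

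- deaths excluded = 100 × *m* × *s*
- observed mortality = (100*m* − 100*ms*) / (100 − 100*ms*)

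| *m* | *s* | Deaths excluded | Observed mortality |
|---|---|---|---|
| 5% | 10% | 0.5 | 4.5 / 99.5 = 4.5% |
| 10% | 25% | 2.5 | 7.5 / 97.5 = 7.7% |
| 20% | 50% | 10 | 10 / 90 = 11.1% |

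This leaves out survivors of an arrest in the ED, for whom there is no basis even for an assumption.

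**4. Illustration of the effect on the AUC (all inputs assumed)**

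For a normally distributed marker, AUC = Φ(d/√2). Suppose d = 0.8 for later deaths (AUC 0.714) and d = 1.2 for the ED arrest deaths (AUC 0.802). The AUC over all deaths is (1 − *s*) × 0.714 + *s* × 0.802: 0.723, 0.736 and 0.758 for *s* = 10%, 25% and 50%. With those deaths excluded it is 0.714. If the marker separated the ED deaths no better than the later ones, the AUC would not change. The direction and size of the bias therefore depend on quantities the documents do not contain.

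**The case against.** The strongest reply concerns usage. The protocol mostly treats ED admission as a moment: vital signs, laboratory tests, imaging, scores and samples are all taken at it (Sections 2.5.2 to 2.5.4). For the interval, Section 2.5.4 speaks of the ED stay. On that usage Table 3 may mean arrest before or at arrival. Listing ED death as an outcome is itself evidence that the authors did not intend to exclude it. This stands as a plausible reading. It does not remove the problem, because *during*, set beside *prior to*, naturally names a further period, and nothing confines it to arrival.

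A second reply is that an arrest exclusion has a reason: the Introduction notes that S100β has been studied in cardiac arrest survivors. That supports excluding arrests before the blood draw. It does not support excluding later ones, since an arrest cannot alter a sample already taken.

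Three stronger inferences are not supported by the documents.

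- A reader might infer that enrolled patients are in fact withdrawn after an arrest. No section says so; it follows only if the criterion covers the ED stay and is applied after enrolment.
- A reader might infer that death is removed from the study. Deaths after leaving the ED remain, as do ED deaths not recorded as an arrest.
- A reader might measure the harm as lost power. Fewer deaths do lower power, but that does not measure selection bias, and the number lost is unknown.

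**Conclusion.** The point holds as an unresolved conflict between Table 3 and Section 2.5.4. If the criterion is applied to the whole ED stay, it makes eligibility depend on a post-baseline event on the path to the outcome and truncates early mortality. If arrest at arrival is meant, the design is sound on this point but the text does not say so. The five hospitals named in Section 2.1 could then treat the same patient differently, one excluding and another counting the death.

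The size cannot be derived. The range of 0.5 to 10 lost deaths per 100 patients rests wholly on the assumed 5–20% mortality and 10–50% share, and it shows only that the effect could be negligible or considerable. The case for acting rests on the conflict and on how little it costs to remove.

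**What to change.** Reconcile the two passages.

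- **Table 3:** limit the criterion to cardiac arrest before the baseline blood sample.
- **Sections 2.5.4 and 2.5.6:** state that every consented, sampled patient stays in the analysis whatever happens later in the ED, and is classified under the existing categories (worsened, deceased, 28-day survival). No separate arrest outcome is needed.

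**Cost.** This is a one-line eligibility amendment plus one sentence on the analysis set. Arrest time relative to sampling must be noted; Section 2.5.2 lists neither time. The abstract says data collection is under way, so some patients may already have been excluded under the present wording and may not be recoverable. Their number should be reported, split by arrest before or after sampling where this is known.
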